#### Baseline characteristics

The baseline characteristics which will be reported for both treatment arms separately are shown in Table 1 [25]. We will not undertake any formal test of comparison between the two groups. For continuous data, we will present mean and standard deviation if normally distributed, or median and interquartile range if the data is skewed. Categorical data will be presented with absolute numbers and percentages.

**Table 1 Tab1:** Baseline characteristics

Characteristic	Lenient rate control (*N* = X)	Strict rate control (*N*= X)
General characteristics		
Age, years		
Female sex–no. (%)		
Site of recruitment		
Holbæk		
Roskilde		
Odense		
Bispebjerg		
Hvidovre		
Duration of atrial fibrillation–weeks		
Median(IQR)		
Previous electrical cardioversion–no. (%)		
Previous valvular heart disease, valvular surgery, or valvular replacement–no. (%)		
Comorbidities		
CHA_2_DS_2_-VASc score–no. (%) [16]^a^		
0 (low)		
1 (low-moderate)		
2 or greater (highest: 9) (moderate-high)		
Diabetes mellitus – no. (%)		
Hypertension – no. (%)		
Chronic obstructive lung disease – no. (%)		
Coronary artery disease – no. (%)		
Valvular heart disease – no. (%)		
Chronic heart failure		
Systolic heart failure – no. (%)		
Diastolic heart failure – no. (%)		
NYHA classification – no. (%)		
Class I		
Class II		
Class III		
Class IV		
Number of heart failure hospitalizations – no. (%)		
Alcohol consumption – no. /week		
Tobacco pack years – no		
Pacemaker or implantable cardioverter-defibrillator – no. (%)		
Symptoms – no. (%)		
Dyspnea		
Fatigue		
Palpitations		
mEHRA score – no. (%)		
Score: 1		
Score: 2a		
Score: 2b		
Score: 3		
Score: 4		
General characteristics		
BMI		
Blood pressure – mm Hg		
Systolic		
Diastolic		
Heart rate at rest – BMP		
Rate control medications in use at baseline – no. (%)		
None		
Metoprolol		
Atenolol		
Bisoprotol		
Carvedilol		
Digoxin		
Digoxin and beta-blocker		
Verapamil		
Verapamil and beta-blocker		
Amiodarone		
Other medications in use – no. (%)		
Diuretic		
Anticoagulants		
Antiplatelets		
Glucagon-like peptide 1 receptor agonists		
Sodium-glucose cotransporter-2 inhibitors		
Angiotensin-converting enzyme inhibitors		
Angiotensin receptor blockers		

^a^Congestive heart failure, hypertension, age ≥ 75 (doubled), diabetes, stroke (doubled), vascular disease, age 65 to 74, and sex category (female). The CHA_2_DS_2_-VASc score is a risk model for anticoagulation decision-making in atrial fibrillation patients [22]

#### Handling of missing data

Missing data will be handled according to the recommendations proposed by Jakobsen and colleagues [22]. In short, we will investigate the possible pattern of missing data. If it is plausible that data are missing at random, and the amount of missing data is between 5 and 40%, we will use multiple imputations as a secondary analysis [22]. If less than 5% of data are missing, we will only use participants with follow-up data.

If necessary, we will perform a best-worst- and a worst-best-case scenario. These two scenarios demonstrate the maximum potential impact of missing data. When assessing continuous data, a “beneficial” outcome will be defined as plus two SDs of the group mean, and a “harmful” outcome defined as minus two SDs of the group mean, both “beneficial” and “harmful” outcomes being fixed imputations [22].

When assessing dichotomous data, it will in a best-worst case scenario be assumed that all the participants lost to follow-up in the lenient intervention arm have had a “beneficial” outcome and all the participants lost to follow-up in the strict intervention arm have had a “harmful” outcome [22], conversely, for the worst-best-case scenario [22].

#### Assessments of underlying statistical assumptions

We will systematically assess underlying statistical assumptions for all statistical analyses [26, 27]. For all regression analyses, both primary and secondary, we will test for major interactions between each covariate and the intervention variable. When assessing for major interactions, we will, in turn, include each possible first-order interaction between included covariates and the intervention variable [26, 27]. For each combination, we will test if the interaction term is significant and assess the effect size. We will only consider that there is evidence of an interaction if the test of interaction is statistically significant after Bonferroni adjusted thresholds (0.05 divided by number of possible interactions (treatment variable interaction with “site,” persistent/permanent, and LVEF (≥ 40% or < 40%) = 0.017)) [26, 27]. If it is concluded that the test of interaction is significant, we will consider both presenting an analysis separately for each site (e.g., for each site if there is significant interaction between the trial intervention and “site”) and an overall analysis including the interaction term in the model [26, 27].

#### Assessments of underlying statistical assumptions for linear regression

We will visually inspect quantile–quantile plots of the residuals [28, 29] to assess if the residuals are normally distributed and use residuals plotted against covariates and fitted values [28, 29] to assess for homogeneity of variances [28, 29]. If the plots show deviations from the model assumptions, we will consider transforming the outcome, e.g., using log transformation or square root and/or use robust standard errors [26, 28, 29].

#### Assessments of underlying statistical assumptions for dichotomous outcomes

We will assess if the deviance divided by the degrees of freedom is significantly larger than 1 to assess for relevant overdispersion. Overdispersion is the presence of greater variability (statistical dispersion) in a data set than would be expected based on a given statistical model, and this case considered using a maximum likelihood estimate of the dispersion parameter [27]. We will, by checking if the number of events is larger than 10 (rule of thumb) per site, consider pooling the data from smaller sites if the number of events is too low [27].

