### Randomization

This trial uses centralized randomization at Open Patient data Explorative Network (OPEN), where varying block sizes unknown to the investigators will be used. Randomization is stratified for (1) site of inclusion, (2) persistent/permanent atrial fibrillation (6 months before inclusion), and (3) left ventricular ejection fraction (LVEF) (≥ 40% or < 40%). Participants are be randomly allocated to the lenient versus the strict rate control strategy arm in an 1:1 ratio [3].

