#### Power estimations of secondary and exploratory outcomes

All power estimations below are based on the sample size estimation of 350 participants. The remaining power estimations can be found in supplemental file 2.

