#### Serious adverse events

Using a proportion of participants with one or more serious adverse events in the control group of 20%, a relative risk reduction of 30%, and a risk of type I error of 5%, we will be able to reject the null hypothesis with probability (power) of 32%.

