##### Analysis of dichotomous data

Dichotomous outcomes will be presented as proportions of participants in each group with the event, as well as relative risks with 95% CIs. Dichotomous outcomes will be analyzed using logistic regression adjusting for “site,” type of atrial fibrillation at inclusion (persistent/permanent), and LVEF (≥ 40% or < 40%) (all as fixed effects). Odds ratios will be transformed to relative risks using the NLCOM command in STATA [8].

An example of a dichotomous data is collected from the following outcome: “Switch to rhythm control therapy.”

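### The deviance/df overdispersion check cannot detect overdispersion in individual yes/no outcomes; it responds to how common the event is and should be deleted

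*SAP article*

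**What the plan says.** Under Analysis of dichotomous data, the model is participant-level logistic regression: "Dichotomous outcomes will be analyzed using logistic regression adjusting for “site,” type of atrial fibrillation at inclusion (persistent/permanent), and LVEF", with all terms as fixed effects. The results are reported per participant: "Dichotomous outcomes will be presented as proportions of participants in each group with the event".

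Under Assessments of underlying statistical assumptions for dichotomous outcomes, the diagnostic is: "We will assess if the deviance divided by the degrees of freedom is significantly larger than 1 to assess for relevant overdispersion". After a definition of overdispersion comes the response to a positive finding: "this case considered using a maximum likelihood estimate of the dispersion parameter".

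The article does not say that data will be grouped by covariate pattern before the deviance is taken. It does not define the dispersion estimate, and it does not commit to rescaling standard errors.

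**The concern.** Comparing deviance/df with 1 has meaning for grouped binomial counts, where the observed spread of the counts can exceed the binomial variance. A single yes/no value has no such freedom: its variance is p(1−p) once p is given. In a logistic model fitted by maximum likelihood to individual data, the deviance reduces to a function of the fitted probabilities alone, so the ratio carries no information about extra variability.

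Two things follow. For uncommon events the check stays silent, and its silence says nothing about model fit. For common events it tends to fire even when the model is exactly right, and an analyst may then alter standard errors that were already correct. The outcomes exposed are the dichotomous secondary and exploratory ones, such as serious adverse events and switch to rhythm control. The discretion would be exercised after seeing data, in a plan written to avoid data-driven choices.

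**Working it through.** **Inputs.** There are 350 participants (Power estimations of secondary and exploratory outcomes), allocated 1:1 (Randomization), so 175 per arm. Table 1 lists five sites. The model has 1 intercept + 1 arm + 4 site + 1 AF type + 1 LVEF = 8 parameters, so df = 350 − 8 = 342. Serious adverse events are assumed at 20% in the control group with a 30% relative reduction, so 0.20 × 0.7 = 14% in the other arm and 17% pooled.

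**The plan's own figure.** The article gives no number for the dispersion check. The one power it states for a dichotomous outcome, 32% for serious adverse events, reproduces:
- SE under the null = √(2 × 0.17 × 0.83/175) = 0.0402
- SE under the alternative = √((0.20 × 0.80 + 0.14 × 0.86)/175) = 0.0400
- z = (0.06 − 1.96 × 0.0402)/0.0400 ≈ −0.47, giving power 32.0%

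**Expected ratio.** The Bernoulli deviance per participant at event rate p is d(p) = −2[p ln p + (1−p) ln(1−p)], and the expected ratio is about d(p) × 350/342. At p = 25%, d = 1.125 and the ratio is 1.15. The one-sided 5% chi-square limit on 342 df corresponds to a ratio of 1.129. By this formula the ratio passes 1 at about 19% and passes 1.129 at about 24%. Its maximum, at 50%, is 2 ln 2 × 350/342 = 1.42.

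**Simulation.** The model was correct, with no treatment effect and 2000 trials per rate. The assumed covariate mix was equal-sized sites, half with each AF type and a quarter with low LVEF. The last column gives AF type and LVEF a log odds ratio of 0.7 each.

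| Event rate | Formula ratio | √ratio | Simulated mean ratio | Flagged | Flagged, prognostic covariates |
|---|---|---|---|---|---|
| 10% | 0.67 | – | 0.64 | 0% | – |
| 17% | 0.93 | – | 0.91 | 0% | – |
| 20% | 1.02 | 1.01 | 1.00 | 0.8% | 0.85% |
| 25% | 1.15 | 1.07 | 1.13 | 52% | 35% |
| 30% | 1.25 | 1.12 | 1.23 | 97% | 91% |
| 40% | 1.38 | 1.17 | 1.35 | 100% | – |
| 50% | 1.42 | 1.19 | – | – | – |

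The simulated means lie slightly below the formula because the fitted covariates absorb some deviance. That is why the flag at 25% is close to a coin toss: the mean ratio there, 1.128, sits at the 1.129 limit.

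**At the assumed serious adverse event rates.** The ratio is 1.024 at 20% and 0.829 at 14%, with average (1.024 + 0.829)/2 = 0.93. The check does not fire.

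**Effect on intervals.** Scaling by √(deviance/df) multiplies standard errors by the √ratio column: 7% wider at 25%, 12% at 30%, 17% at 40%, and at most 19% at 50%. If scaling followed a flag, the simulated type I error would be about 3.5% at a 30% event rate (5.3% unscaled) and 3.0% at 40% (6.5% unscaled), with simulation error of about 0.5 points. The Pearson ratio is about 1.02 at every simulated rate, so Pearson scaling changes standard errors by only √1.02 − 1 ≈ 1%.

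**Grouped alternative.** There are 2 × 5 × 2 × 2 = 40 patterns of arm, site, AF type and LVEF, or 350/40 ≈ 9 participants per cell. The grouped deviance test flags 6–16% of correct models, and up to 19% with prognostic covariates.

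**The case against.** A reader might infer that the plan will inflate standard errors whenever the event rate exceeds about 25%. The text does not support that:
- The response is only considered, and the estimator is not defined. The widening figures assume deviance scaling.
- At 25% the flag appears in 35–52% of simulated trials; it becomes near-certain only from about 30%.
- The only event rate given in the article for a dichotomous outcome is that for serious adverse events, and there the check is silent. No dichotomous outcome in the article is given an assumed rate above 25%.
- A reader might also count hospital admissions among the affected outcomes, but their number is count data analysed by van Elteren's test.

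It can further be said that every model term is categorical, so the analysts could group the data and give the check meaning. The error would also be conservative, and confined to outcomes the article calls hypothesis-generating.

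All of this limits the consequence, and it stands. It does not rescue the diagnostic. Nothing in the article says the data are grouped, and the grouped version is itself poorly calibrated at this sample size. A check that is silent or fires according to event frequency gives no valid assurance either way.

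**Conclusion.** The check as written is uninformative for the individual yes/no outcomes it is meant to assess. That part is a mathematical property of the model and needs no assumption about event rates. The flag frequencies assume 350 participants, eight parameters, a one-sided 5% chi-square test and the covariate mix stated above. The widening of 7% to 19% is conditional on two further steps that the plan leaves open: acting on the flag, and doing so by deviance scaling.

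The primary outcome is analysed by linear regression with its own checks, so the primary conclusion is unaffected. This is a low-severity correction.

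**What to change.** In Assessments of underlying statistical assumptions for dichotomous outcomes, delete the deviance/df rule and the sentence that defines overdispersion and introduces the dispersion parameter. The rule on events per site can stay. If a fit check is wanted, specify a calibration check, for example observed against predicted event counts across bands of fitted risk. Use it as a diagnostic only, and state that standard errors will not be rescaled. A deviance test grouped by covariate pattern is not a good substitute at about 9 participants per cell.

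The cost is two deleted sentences, and one added if a calibration check is kept. Data collection, sample size and the primary analysis do not change.

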#### Statistical reports

Blinded data will be sent to OPEN for blinded data management [3]. Statistical analyses will be performed with the two intervention groups coded as “A” and “B” by two independent blinded statisticians [3]. Two blinded conclusions will be drawn by the steering group: one assuming “A” is the experimental group and “B” is the control group—and one assuming the opposite. Based on these two blinded conclusions, two abstracts will be written (will be published as a supplement to the main publication) [3]. When the blinding is broken, the “correct” abstract will be chosen, and the conclusions in this abstract will not be revised [3].

## Discussion

To prevent bias arising from selective reporting and data-driven analyses, we present this pre-defined description of the statistical analysis plan of the DanAF trial.

### Strengths

Our analysis plan has several strengths. We have predefined our analysis plan and this will reduce outcome reporting bias and data-driven results. Our conclusions will be based on only one primary outcome, i.e., quality of life (measured using SF-36 physical component score) which is a patient-important outcome and is therefore of high relevance to the patients and the clinicians when choosing treatment. Our sample size estimation is based on similar studies assessing the quality of life and studies assessing minimal important differences [15–17]. Our other secondary, exploratory, and echocardiographic outcomes will be hypothesis-generating only; hence, problems regarding multiplicity will be limited (see the “Limitations” section). The inclusion and exclusion criteria of this trial are few, which should increase the external validity of our trial.

We have performed a sample size estimation based on previous evidence [15–17]. With realistic intervention effects, we will adjust the thresholds for statistical significance and the confidence intervals if the sample size is not reached [3]. In Denmark, a complete follow-up of all participants for death and hospitalizations is possible, as all residents are issued a permanent unique civil registration number at birth or immigration that enables individual-level linkage between administrative registries [3]. If necessary, we will use multiple imputation and best–worst/worst-best-case scenarios to assess the potential impact of the missing data on the results [22]. Furthermore, we plan to systematically assess whether underlying statistical assumptions are fulfilled for all statistical analyses.

Hence, our trial will be conducted with low risks of both random errors (“play of chance”) and systematic errors (“bias”) [3, 18, 30].

### Limitations

Our analysis plan also has limitations. According to our power estimations, the number of recruited participants will most likely not allow us to conclude on outcomes such as mortality or serious adverse events [3]. Therefore, even if one of the interventions turns out to be superior in terms of quality of life, it will be uncertain how the trial interventions influence hard outcomes such as, e.g., death. This will be explored in a future meta-analysis with individual patient data from the RACE II trial [16]. The consequence may ultimately be that a superiority trial in terms of “hard outcomes” is needed [3].

The results of the EAST trial [31] are expected to delay when rhythm control is abandoned for rate control only. This may impact on the generalizability of our results as some participants who are now included in DanAF may in the future instead be treated with rhythm control [3].

Yet another limitation is that participants presumably will receive different medications and procedures in the compared groups [3]. If we show a difference (or lack of a difference) between the groups, it will be difficult to interpret what part of the treatment algorithm for reaching a certain rate target that caused this difference [3].

## Data Availability

Region Zealand is the data controller. Steering committee members have access to all data. Anonymized data will be made available in a file repository. All data regarding the statistical analysis plan is available in the present publication.
